### Prostate Biopsy

All patients will undergo ultrasound-guided transperineal prostate biopsy when the 6-month post H-FIRE MRI report is deposited to get the sample of the prostate for assessing the efficiency of H-FIRE. We will sample both the ablation region and the untreated area to minimize missed tumors. The combined biopsy will be performed under local anesthesia with a two- or three-step procedure after reviewing the MRI image and report. Firstly, a cognitive fusion-targeted biopsy will be taken with three cores for each ablation area. Secondly, another targeted biopsy with three cores for each suspicious lesion will be taken only when there is some finding with a PI-RADS score more or equal to 3 on the MRI (13). Lastly, a 12- to 20-region systematic template-guided biopsy will follow (12). The template-guided biopsy region will be a little different between the centers but will be the same as the pre H-FIRE biopsy and the same within the same center.

### Calculation of Sample Size

The detection rate of significant cancer after focal therapy is clinically acceptable to be 20% (14). The previous data from the Changhai hospital showed the detection rate of significant cancer after ablation to be 9%.

For the single arm OPC hypothesis, employing 80% power, 2.5% one-sided α, and a 95% two-sided confidence interval, 87 men will be required. Assuming there is a 20% withdrawal/loss in follow-up, 110 participants are expected to be enrolled.

### Statistical Methods

All statistical tests will use a two-sided test. p values less than or equal to 0.05 will be considered statistically significant (except for special instructions). In addition to point estimation, 95% confidence intervals will be calculated for all results. All continuous variables will be described using the mean, standard deviation, median, minimum, maximum, first quartile (Q1), and third quartile (Q3), and categorical variables will be described using frequencies and proportions. Appropriate methods will be used to analyze the comparison according to the types of variables. Student’s t test or Wilcoxon signed-rank test will be used for the comparison of quantitative data between groups; chi-square test or Fisher’s exact test will be used for categorical data; and Wilcoxon signed rank test or Cochran–Mantel–Haenszel (CMH) test will be used for ranked data.

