To maintain the efficacy and avoid the side effect of the current pathway, a selective pathway between active surveillance and radical treatment is emerging, which is known as focal therapy. This pathway aims to destroy the focal cancer lesions and preserve the surrounding benign tissue. There are various energy sources that have been used for focal therapy. The prevalent type of energy is thermal energy, including high-intensity focused ultrasound (HIFU), laser, and cryotherapy, which lead to lethal effects by generating extreme temperatures (4). Another novel nonthermal technique for ablation is irreversible electroporation (IRE), which delivers pulsed high voltage, but the low-energy direct electric current through the specialized electrode needles generates a short and intense electrical field to the cell membrane, thereby invoking cell death (5). The potential advantage of IRE seems to be tissue-selective with little damage to the connective tissue structure (6). That is to say, some vital structures like blood vessels or nerves may be reserved after an ablation procedure (6, 7). The traditional IRE applies 80 to 120 unipolar pulses with a pulse of 50 to 100 μs and an electric field >1,000 V/cm. However, this typical IRE protocol may evoke muscle contraction during the procedure, leading to pain for the patients and causing displacement of the electrode needles. Recently, a new type of IRE technique called high-frequency IRE (H-FIRE) has emerged (8). H-FIRE utilizes a set of bipolar pulse burst. Each burst consists of some individual pulses range from 0.5 to 10 μs, and the total time of a single burst is up to 100 μs. Some animal experiments had verified the efficacy of H-FIRE in tumor killing and reduction in muscle contraction. We also preliminarily confirmed that H-FIRE could preserve the urethra and major vasculature in the prostate in the human pilot trial (9).

This multicenter trial aims to evaluate the efficacy and safety of H-FIRE ablation for men with localized prostate cancer. The primary objective is to determine if the clinically significant cancer is detected by less than 20% by prostate biopsy after the ablation.

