### Outcomes

The primary outcome is the detection rate of clinically significant prostate cancer, defined as any biopsy core with a Gleason score of 3 + 4 or more, or a Gleason score of 3 + 3 plus maximum cancer core length at >3 mm, or an increase from the original cancer burden in the ablation area 6 months post H-FIRE.

The main secondary objectives are as follows:

To assess the proportion of men with serum PSA level at >2 ng/ml over the nadir in 6 months post H-FIRE;To assess the adverse events according to Common Terminology Criteria for Adverse Events (CTCAE) at any time post H-FIRE;To assess the proportion of men using pads preoperative and 1 months, 3 months, and 6 months post H-FIRE;To assess the urinary symptoms by questionnaire of International Prostate Symptom Score (IPSS) scoring preoperative and 1 months, 3 months, and 6 months post H-FIRE;To assess the erectile symptoms by International Index of Erectile Function (IIEF-5) scoring preoperative and 1 months, 3 months, and 6 months post H-FIRE; andTo assess the time of urinary catheter retention.

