### Trial Design

This prospective, multicenter and single-arm objective performance criteria (OPC) trial will take place at four academic medical centers in China: Changhai Hospital, Shanghai; Renji Hospital, Shanghai; Peking Union Medical College Hospital, Beijing; and Changzheng Hospital, Shanghai. The main objective of this study is to assess the efficacy and safety of high-frequency irreversible electroporation (H-FIRE) for the ablation of prostate cancer. All participants who meet the entry criteria will undergo H-FIRE and subsequently receive prostate biopsy 6 months later (**Figure 1**). This trial is approved by the committee for medical and health ethics of all centers and registered on ClinicalTrials.gov (NCT03838432).

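### Statistical Methods describes between-group tests in a one-arm trial, and gives pad use, measured repeatedly in the same men, only independent-sample tests

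*Protocol article*

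**What the plan says.** All places are in the protocol article.

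- **Trial Design** calls the study a "prospective, multicenter and single-arm objective performance criteria (OPC) trial" and adds: "All participants who meet the entry criteria will undergo H-FIRE and subsequently receive prostate biopsy 6 months later". No comparison arm is described.
- **Introduction** gives the primary aim: "The primary objective is to determine if the clinically significant cancer is detected by less than 20% by prostate biopsy after the ablation".
- **Calculation of Sample Size** takes 20% as the acceptable rate and 9% as the expected rate. With 80% power, one-sided 2.5% and a two-sided 95% confidence interval, it arrives at 87 men, or 110 after 20% loss.
- **Outcomes** lists pad use as a secondary objective: "To assess the proportion of men using pads preoperative and 1 months, 3 months, and 6 months post H-FIRE". IPSS and IIEF-5 have the same four time points.
- **Statistical Methods** says that Student's t or Wilcoxon signed-rank "will be used for the comparison of quantitative data between groups". It then says that chi-square or Fisher's "exact test will be used for categorical data", and gives ranked data to signed-rank or Cochran–Mantel–Haenszel (CMH). Tests are two-sided at 0.05 unless specially instructed, and every result is to have a 95% confidence interval.

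**The concern.** The design calls for two kinds of inference: one proportion against a fixed 20%, and the same men before and after treatment. The listed tests are worded for a third kind, a comparison of groups, which the trial does not contain.

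The mismatch is clearest for pad use. It is a yes/no outcome in the same men at four visits, and the only tests given for categorical data normally assume that the two samples are different people. No paired test for binary data is named. Ignoring a positive within-man correlation makes a pre/post comparison conservative. In a study partly about safety, that means a worsening is harder to detect.

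For the scores, the sentence contradicts itself by naming a paired test for a between-group comparison. For the primary outcome, the one-sample test on which the sample size rests is not named, so the interval method that decides success is open.

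**Working it through.** **1. The plan's own sample size.** Inputs from Calculation of Sample Size: p0 = 0.20, p1 = 0.09, one-sided alpha 0.025, power 0.80.

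n = [1.960·√(0.20·0.80) + 0.842·√(0.09·0.91)]² / (0.20 − 0.09)² = 86.8, rounded up to 87.

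Allowing for loss: 87/0.80 = 108.75, so 109 against the stated 110. Both figures reproduce. The formula is the one-sample score (normal-approximation) test, so the trial is sized for a test that Statistical Methods does not name.

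**2. What the open interval method changes at n = 87.** Success means that the upper limit of the two-sided 95% interval is below 20%.

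| Method | Most detections allowed | Upper limit | Exact one-sided error at 20% | Power at 9% |
|---|---|---|---|---|
| Exact (Clopper–Pearson) | 9 | 18.7% | 1.25% | 74.4% |
| Score (Wilson) | 10 | 19.9% | 2.66% | 84.2% |
| Wald | 11 | 19.6% | 5.1% | 91.0% |

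A chi-square goodness-of-fit test against 20% gives two-sided p = 0.047 at 10/87 and 0.086 at 11/87, the same limit as the score interval.

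Exact power moves in steps: 83.3% at 88 men, 79.6% at 92, 78.6% at 93, and at least 80% from 94 on. With 110 enrolled and 20% lost, 110 × 0.80 = 88 men remain.

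**3. Pad use, illustration only.** The document gives no pad rates. Assume 88 men, with 2 users before and 8 at 6 months. As independent samples (2/88 v 8/88), Fisher gives p = 0.099 and uncorrected chi-square 0.051. Exact McNemar uses only the men who change, and the same margins allow three splits:

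- 6 new, 0 resolved: 2 × (1/2)⁶ = 0.031
- 7 new, 1 resolved: 2 × (1 + 8)/2⁸ = 0.070
- 8 new, 2 resolved: 2 × (1 + 10 + 45)/2¹⁰ = 0.109

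The independent-sample tests return the same p value for all three, because they do not see who changed.

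**4. Scores, only if the t test were run unpaired.** The unpaired standard error is SD·√(2/n); the paired one is SD·√(2(1 − ρ)/n). Their ratio is 1/√(1 − ρ): 1.41 at ρ = 0.5 and 1.83 at ρ = 0.7. For n = 87 and an assumed shift of 0.3 SD:

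| Assumed ρ | True error of a nominal 5% unpaired test | Power unpaired | Power paired |
|---|---|---|---|
| 0.3 | 1.9% | 51% | 66% |
| 0.5 | 0.6% | 51% | 80% |
| 0.7 | 0.03% | 51% | 95% |

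The correlations and the shift are assumptions.

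**The case against.** **Scores.** A reader might infer that IPSS and IIEF-5 will be analysed as if they came from different men. The text does not support that. Signed-rank is listed for both quantitative and ranked data and is a paired or one-sample test, and Student's t has a paired form. The power losses in step 4 therefore follow only from a reading that the document does not fix.

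**Primary outcome.** A reader might also infer that the primary hypothesis has no matching test. That goes too far as well. The sample-size section gives the one-arm hypothesis, the one-sided level and the two-sided 95% interval, and Statistical Methods requires such intervals throughout. Together they imply comparing the upper limit with 20%. The between-group phrase is attached to quantitative data only, and a goodness-of-fit chi-square could serve as the test. Two-sided 5% is compatible with one-sided 2.5%. Interval details are often left to an analysis plan, so their absence alone is no fault.

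**Pad use.** The pad example rests on invented counts, and with 8 new and 2 resolved the paired p value exceeds Fisher's. Outcomes says only that pad use will be assessed, with no stated hypothesis, so no trial decision hangs on its p value. All of this stands, and it limits the size of the point.

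It does not remove it. The between-group wording contradicts the design, and the rule for categorical data is stated, not merely absent. An analysis plan that paired the pad data would have to depart from it. CMH can be stratified by patient, but it is listed for ranked data, and the pad outcome is a proportion.

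**Conclusion.** The point holds in a limited form. Statistical Methods describes a comparison that a one-arm trial cannot make, names a paired test for it, does not say which t test is meant, and sends repeated pad use to tests that in their usual form ignore pairing. The pad-use rule is the part that does not fit. The score analyses and the primary decision are unclear, not shown to be wrong.

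It would be tempting to conclude that the plan will hide new incontinence. The document does not show this: the gain from pairing depends on the discordant split or the within-man correlation, and neither is given. The p values and power figures in steps 3 and 4 are illustrations.

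Step 2 rests on the plan's own inputs. At 87 men the unnamed interval method moves the success limit between 9 and 11 detections, which is reason enough to name it.

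**What to change.** Reword Statistical Methods as follows.

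1. Delete the between-group phrase and state that comparisons with baseline are within-patient.
2. IPSS and IIEF-5: paired t or signed-rank on the change from baseline.
3. Pad use: exact McNemar for each visit against baseline, or a repeated-measures model for binary data.
4. Primary outcome: a one-sample test of the detection rate against 20% at one-sided 2.5%, met if the upper limit of the two-sided 95% interval is below 20%. Name the interval method and match it to the sample size. The score method underlies 87. If an exact interval is preferred, state that power is 74.4% at 87 men and 83.3% at the 88 expected from 110 enrolled, and that it dips below 80% again at 92 and 93.

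The cost is a wording change in the protocol or analysis plan, made before the data are analysed. It needs no new data. It needs no more patients unless an exact interval is chosen and 80% power is wanted at every evaluable number that might arise, which requires at least 94 evaluable men.

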### Irreversible Electroporation Strategy and Procedure

The ablation area will be planed following an extended ablation strategy (**Figure 2**), which depends on both biopsy and MRI results. The whole procedure of H-FIRE will be performed under general anesthesia with full-muscle paralysis to avoid contractions, employing the composite steep pulse therapeutic apparatus (**Figure 3**) manufactured by REMEDINE company. With the guidance of a biplanar TRUS probe, the electrode needle will be placed to the target lesion by getting through a 5-mm brachytherapy template grid and the perineum (**Figure 4**). The electrode needles will be placed as follows (**Figure 5**): (1) one needle will be placed in the center of the targeted lesion, and three or four needles will be positioned around the lesion; (2) the distance of each needle is between 0.5 and 2.0 cm; and (3) the maximum electrode exposure length ranges from 0.5 to 4.0 cm, in order to penetrate the whole prostate. After placing the needle, the device will be set to deliver predefined pulses for every targeted two needles. The entire procedure is expected to last 40 to 120 min, depending on the total pulse number, which was confirmed by the size and shape of the lesions to be ablated.

**Figure 2 f2:**
[figure not shown]
Ablation strategy. Ablation every lesions; every ablation area includes the tumor and some surrounding benign tissues (the safety margin is >1 cm).

**Figure 3 f3:**
[figure not shown]
The composite steep pulse therapeutic apparatus (REMEDINE, Shanghai, China).

**Figure 4 f4:**
[figure not shown]
Electrode needles are placed through a brachytherapy template grid and the perineum.

**Figure 5 f5:**
[figure not shown]
Electrode needle placement. **(A)** Coronal view: one needle is positioned in the center of the targeted lesion, and three to four needles are positioned around the lesion; the distance between each needle ranges 0.5–2.0 cm. **(B)** Sagittal view: maximum electrode exposure length covers the whole length of the prostate (from apex to base).

### Monitoring

A team of independent clinical research associates (CRA) with all more than 5 years of experience is responsible for being familiar with the trial protocol and monitoring all researchers and all participants involved in the whole process of this trial. The CRA’s role is to (1) monitor the trial plan, the record forms, and the case report form before the start of the trial; (2) monitor participants’ informed consent and enrolment rates; (3) monitor the compliance of participants and investigators with the protocol; (4) monitor the data quality and authenticity; (5) monitor adverse events and serious adverse events; and (6) monitor the device supplied, installed, and reclaimed by relevant regulations.

### Harms and Adverse Events

All harm relevant or not relevant to the procedure of H-FIRE will be recorded, including (1) suspected adverse effects related to the IRE device; (2) obvious non-related diseases that do not appear before the trial; (3) deterioration of existing conditions; (4) accidental injury; (5) adverse events caused by improper use of the device; and (6) any adverse events caused by user error. The adverse events during the trial will be evaluated according to Common Terminology Criteria for Adverse Events (CTCAE), which is widely used as a standard for severity grading scale in clinical trials. The serious adverse events include (1) deaths; (2) fatal illness or injury; (3) permanent defects in body structure or body function; and (4) requirement of hospitalization or prolonged hospitalization. Harms and adverse events will be recorded from the beginning of the trial to 1 month after the biopsy. All AEs and SAEs will be recorded by a CRA team member immediately and reported to the ethics committee and the department of quality supervision and control within 24 h.

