### Clinical Pathway

Participants will be hospitalized 1 day before the IRE. The IRE will be performed *via* the perineum with the guidance of ultrasound under general anesthesia. A Foley catheter and prophylactic antibiotics will be given to patients after the procedure. All participants will be scheduled to be dismissed the following day after IRE. After discharge, the patient will take 1 week of antibiotics, alpha1-adrenoceptor antagonists, and painkillers. The catheter will be retained for 3 to 14 days according to the ablation range and area and will be withdrawn at the outpatient clinic. If the patient is unable to void after removing the catheter, he will be given another Foley catheter for 1 more week.

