### Follow-Up and Study Endpoint

MRI will be organized 1 and 6 months after IRE, and serum PSA measurement will be organized 1, 3, and 6 months. Patients will be scheduled to respond the questionnaires including I-PSS, IIEF-5, and pad usage records at 1, 3, and 6 months. At 6 months, all participants will receive a prostate biopsy to get the sample for pathological evaluation. The details and timeframe of follow-up are shown in **Table 2**. This trial will discontinue due to the following: (1) more than 20% of the total number of cases deviated from the protocol; (2) the number of dropout cases exceeds 20% of the total number of designed cases; (3) the severity and frequency of serious adverse events that occurred tended to exceed those reported in local treatment literature; and (4) the severity and frequency of instrument defects and faults exceed the acceptable risk.

**Table 2 T2:** Participant timeline in the study.

	Contact with patient					
	Vist 1	Vist 2	Vist 3	Vist 4	Vist 5	Vist 6
	Pre H-FIRE	H-FIRE	1-week post H-FIRE	1-month post H-FIRE	3-month post H-FIRE	6-month post H-FIRE
Time	-30~0 days	0	7~10 days	4~6 weeks	12~14 weeks	6~7 months
Consent	×					
Screening	×					
Baseline characteristic	×					
PSA	×			×	×	×
Routine blood test	×		×	×	×	×
Routine urine test	×		×	×	×	×
Blood biochemistry test	×		×	×	×	×
ECT	×					
Performance status	×					
MRI	×		×			×
Prostate biopsy	×					×
Pathological assessment	×					×
NCCN risk assessment	×					
Clinical stage assessment	×					
Pad usage record	×			×	×	×
IIEF–5 scoring questionnaire	×			×	×	×
IPSS scoring questionnaire	×			×	×	×
Urinary catheter removed			×			
Withdrawal	Complete as required at any time following registration					
SAE	Complete as required at any time following registration					

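### SAE criterion (2) repeats criterion (1), so a survived life-threatening event that leaves no permanent defect and causes no new or longer hospital stay falls outside the SAE definition and discontinuation rule (3)

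*Protocol article*

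**What the plan says.** Under Harms and Adverse Events, the protocol article defines seriousness by a numbered list of four. It begins "The serious adverse events include (1) deaths; (2) fatal illness or injury" and ends with "3) permanent defects in body structure or body function; and (4) requirement of hospitalization or prolonged hospitalization".

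The same section covers adverse events in general. On grading, it says "The adverse events during the trial will be evaluated according to Common Terminology Criteria for Adverse Events (CTCAE"). On reporting, it says "All AEs and SAEs will be recorded by a CRA team member immediately and reported to the ethics committee" and to the quality supervision department within 24 h.

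Two other sections bear on the point:

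- **Clinical Pathway** fixes the planned stay: "Participants will be hospitalized 1 day before the IRE" and "All participants will be scheduled to be dismissed the following day after IRE".
- **Follow-Up and Study Endpoint** gives four grounds for discontinuing the trial. The third is that "the severity and frequency of serious adverse events that occurred tended to exceed those reported in local treatment literature".

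**The concern.** A list of four separately numbered criteria should have four different contents. Here the first two coincide: an illness or injury that is fatal is a death. The item that could have covered danger to life without death therefore covers nothing of its own.

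This matters because classification has a consequence in this trial. The third discontinuation rule is worded on serious adverse events, not on all adverse events. A non-fatal event that put a man's life at risk around an ablation under general anesthesia is evidence that such a rule should be able to weigh. If the event meets none of the four criteria, the rule as worded does not reach it. Four centers would also have no common text from which to decide how to classify it.

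**Working it through.** The article states no figure on this point, so the check is a reading of the definition against the planned stay and the discontinuation rule.

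**Step 1: what criterion (2) adds.** Every fatal illness or injury falls under criterion (1). A looser reading, an illness expected to end in death, still leaves out an illness that the patient survives. Criterion (2) therefore brings in no survived event.

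**Step 2: the planned stay.** Take the procedure as day 0. Admission is on day −1 and planned discharge on day +1. An event on day 0 that delays discharge beyond day +1 is a prolonged hospitalization and meets criterion (4).

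**Step 3: each kind of life-threatening event against the four criteria as written.**

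| Life-threatening event | Criterion met | SAE? | Within the wording of rule (3)? |
|---|---|---|---|
| Patient dies | (1), and (2) again | Yes | Yes |
| Survived, permanent defect | (3) | Yes | Yes |
| Survived, discharge delayed beyond day +1 | (4) | Yes | Yes |
| Survived, after discharge, readmitted | (4) | Yes | Yes |
| Survived during the planned stay, no permanent defect, discharged on schedule | none | No | No |
| Survived after discharge, no permanent defect, treated without admission | none | No | No |

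The gap is the last two rows.

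**Step 4: what happens to an event in the gap.** It is recorded, evaluated by CTCAE and reported within 24 h, because the reporting sentence covers AEs as well as SAEs. CTCAE evaluation does not make it serious, since the article ties no CTCAE grade to the SAE definition. The participant timeline (Table 2) has a row for SAEs and none for other AEs. The event is therefore visible to the ethics committee but is not among the events that rule (3) names.

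**Step 5: size.** The number of events in the last two rows would be the number of men treated times the rate of such events. The article gives no such rate, so no number can be derived, and it could be zero. The article's one computed figure, the sample size (87, raised to 110 for dropout), does not depend on the SAE definition.

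**The case against.** **Most such events are caught anyway.** This stands, and it sets the limits of the point. A reader might infer from the duplicated item that any survived life-threatening event during the index admission meets no SAE criterion. The article does not support that: criterion (4) takes in any event that delays the next-day discharge, and criterion (3) any that leaves a permanent defect. Only the remainder is missed.

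**The wording may be a slip, or the list may be open.** Both are plausible. The authors numbered the two items separately, which suggests that they meant the second to be different, and the list is introduced by a verb that need not be exhaustive. The text settles neither. If it is a slip, it needs the same correction. If the list is open, nothing tells the centers what else belongs on it. The full protocol and case report form are not shown and may be worded better. But this is a definition that the article states, not a detail that it leaves out.

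**The safety results are unaffected.** This stands. A reader might infer that the trial's safety outcome is undercounted. SAE frequency is not a listed outcome; the secondary objectives name adverse events by CTCAE, and an event in the gap is still included there.

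**The discontinuation rule is a judgment.** This also stands. Rule (3) sets no numeric threshold and speaks of a tendency to exceed the literature. It cannot be shown that one unclassified event would change a decision, and those who receive the 24 h reports could still act on it. What remains is that the rule, as worded, does not include the event.

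**Conclusion.** The point holds in a narrow form. As written, criterion (2) duplicates criterion (1), and no criterion covers a survived life-threatening event as such. An event of that kind is not an SAE, and lies outside the wording of discontinuation rule (3), when it leaves no permanent defect and causes no new or prolonged hospitalization. It is not lost to safety reporting or to the CTCAE adverse event outcome.

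The size cannot be stated. No event rate is given, rule (3) has no threshold against which to measure a shift, and the gap is probably small given the next-day discharge. The conclusion rests on two assumptions: that the text is read literally, and that the four listed items are the whole definition. The correction is worth making because the definition feeds a rule for discontinuing the trial and changing it costs almost nothing.

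**What to change.** 1. Reword criterion (2) so that it is distinct from criterion (1) and covers life-threatening illness or injury. Criteria (1), (3) and (4) can stay as they are.
2. Put the same wording in the case report form, so that the four centers classify alike.
3. Reconcile the definition with the third discontinuation rule under Follow-Up and Study Endpoint, by stating there that serious adverse events are those so defined.

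If the full protocol and case report form already carry a distinct second criterion, only the published text needs correcting.

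The cost is one phrase in the protocol and one in the case report form, plus a cross-reference. The sample size and the primary analysis do not change. The one downside is that the SAE count may be slightly higher.
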